## Abstract

**Objectives:**

In low/middle-income countries (LMICs), more than half of patients with first-episode psychosis initially seek treatment from traditional and religious healers as their first care. This contributes to an excessively long duration of untreated psychosis (DUP). There is a need for culturally appropriate interventions to involve traditional and spiritual healers to work collaboratively with primary care practitioners and psychiatrists through task-shifting for early detection, referral and treatment of first episode of psychosis.

**Methods:**

To prevent the consequences of long DUP in adolescents in LMICs, we aim to develop and pilot test a culturally appropriate and context-bespoke intervention. *T*raditional *HE*alers working with primary care and mental *H*ealth for early interventi*O*n in *P*sychosis in young p*E*rsons (THE HOPE) will be developed using ethnographic and qualitative methods with traditional healers and caregivers. We will conduct a randomised controlled cluster feasibility trial with a nested qualitative study to assess study recruitment and acceptability of the intervention. Ninety-three union councils in district Peshawar, Pakistan will be randomised and allocated using a 1:1 ratio to either intervention arm (THE HOPE) or enhanced treatment as usual and stratified by urban/rural setting. Data on feasibility outcomes will be collected at baseline and follow-up. Patients, carers, clinicians and policymakers will be interviewed to ascertain their views about the intervention. The decision to proceed to the phase III trial will be based on prespecified stop–go criteria.

**Ethics and dissemination:**

Ethical approval has been obtained from Keele University Ethical Review Panel (ref: MH210177), Khyber Medical University Ethical Review Board (ref: DIR/KMU-EB/IG/001005) and National Bioethics Committee Pakistan (ref no. 4-87/NBC-840/22/621). The results of THE HOPE feasibility trial will be reported in peer-reviewed journals and academic conferences and disseminated to local stakeholders and policymakers.

**Trial registration number:**

ISRCTN75347421.

STRENGTHS AND LIMITATIONS OF THIS STUDYThe proposed study seeks to develop and pilot test a novel and culturally appropriate intervention for early detection, referral and treatment of first episode of psychosis with the aid of traditional spiritual healers to prevent consequences of untreated psychosis in resource-limited settings.The present study aims to integrate mental health and primary care services to provide early intervention in untreated psychosis in collaboration with traditional healers and evaluate it in a feasibility randomised controlled trial (RCT).We will use a mixed-methods design, comprising both quantitative and qualitative methods, to develop, test and evaluate the feasibility of the intervention and understand its strengths and limitations.A limitation of this feasibility cluster RCT is that the planned study has a small study and is not powered to test the effectiveness of the intervention. This being a feasibility trial will evaluate the acceptability of the intervention and will provide precision estimates for an adequately powered definitive RCT in future.

## Introduction

### Background and rationale

First-episode psychosis (FEP) has peak onset between 15 and 35 years of age.^1–3^ FEP can disrupt education, reduce long-term employment, cause huge economic burden and is associated with significantly higher mortality as compared with the general population.^4^ Duration of untreated psychosis (DUP), the period between the onset of psychosis and initiating treatment, is 125 weeks in low/middle-income countries (LMICs) compared with 62.5 weeks in high-income countries (HICs).^5^ Even when initiated, the treatment is mostly limited to acute episodes resulting in a huge treatment gap with around 70% of people not receiving regular care^6 7^ with incidence of self-harm during long periods of untreated psychosis.^5^

A major factor for the long DUP in LMICs is the preference of the majority of the patients to see traditional and spiritual healers (TSHs) as their first care providers for mental disorders.^8^ This is consistent with a systematic review showing predominantly supernatural explanatory models of illness for psychosis in LMICs.^9^ Research with TSHs in Pakistan^10–12^ has identified that the following terms are used for identifying people suffering from psychosis: influence of jinn, saya (influence or shadow), ‘strong spell or under the control of spirits’ lewanay (insane) and ‘superstitious’. This is consistent with previous literature.^11 12^ These healers use different methods of treatment, including de-possession from jinn or saya, instruction and advice regarding prayers, Tawiz (symbolic lines and verses written on a piece of paper), Dam (holy verses recited and blown on the body), Dua (prayers) and special religious ceremonies, which include reciting holy verses loudly and family accompanying the spiritual healers in a trance-like state and exorcism to remove the spirits from home and offering holy water.^11 12^ Other methods for treatment include homoeopathy, danyalism (shamanism), the holy Tabbarak (blessed food), sugar or salt, and drinking Dam Wala Pani (sacred verses recited on water) available at Dargahs (shrines).^12 13^

Another key factor in the long DUP is the lack of primary care involvement in the treatment of psychosis.^14^ The integration of mental health and primary care services is widely advocated, especially in LMICs, and primary care practitioners have an important role in providing effective early intervention in psychosis.^15^ However, the evidence suggests that primary care physicians (PCPs) have practically no role in the treatment of psychosis in LMICs.^14^

Evidence available in other disease areas, such as HIV/AIDS, suggests that with appropriate training and support, services have been scaled up in collaboration with traditional healers.^16^ However, there are hardly any interventions for improving collaboration with TSHs in mental health. A systematic review on the effectiveness of TSHs in treating mental disorders highlighted limited interventions mostly described in generally poor-quality studies with no intervention found involving TSHs in the care of FEP.^17^ There is an urgent need to work collaboratively with TSHs and develop and rigorously evaluate early intervention in psychosis interventions in LMICs, as TSHs have far greater influence in treating mental disorders, and a pilot study showed that TSHs are open to identifying and referring individuals with possible psychosis.^18^

### Aims and objectives

To prevent the consequences of long DUP in young persons in LMICs, we aim to develop and pilot test a culturally appropriate and context-bespoke intervention (Traditional HEalers working with primary care and mental Health for early interventiOn in Psychosis in young pErsons (THE HOPE)) for early identification, referral and management of FEP in the young population in Peshawar, Khyber Pakhtunkhwa (KP) in Pakistan and evaluate its feasibility for implementation. THE HOPE intervention will involve TSHs working collaboratively with primary care practitioners and psychiatrists through task-shifting for early detection, referral and treatment of FEP.

#### Objectives

To co-develop with key stakeholders a culturally appropriate intervention for early identification, referral and management of FEP.To investigate the acceptability of task-sharing and training procedures, and to establish pathways for referral and management of FEP in consultation with all stakeholders.To establish the feasibility and acceptability of involving mental health service users in training and feasibility study methods.To evaluate the acceptability and feasibility of THE HOPE in terms of changes in knowledge and referral to mental health services by TSH and users’ satisfaction.To estimate the parameters (eg, recruitment and retention rates), means and standard deviations of the key outcome measures to benchmark potential outcome measures and enable sample size calculations for future pragmatic randomised controlled trials (RCTs).To assess the best methods for implementing and evaluating the intervention in the healthcare system.

## Methods and analysis

The research plan for THE HOPE Study includes a development phase to robustly co-design and co-produce THE HOPE intervention following the Medical Research Council framework for developing and evaluating complex interventions.^19^ This paper describes in detail the methodology of the pragmatic cluster pilot RCT and the intervention development process is given here briefly.

The intervention will be co-developed working with TSHs, PCPs and service users through a series of (1) culturally appropriate interactive community engagement activities, (2) ethnographic studies and (3) qualitative studies. Trained ethnographers will participate in up to 15 different communal settings involving interactions with TSHs, healthcare workers, patients and carers. Ethnographic data will provide insights for intervention development and will inform about disease awareness and indigenous knowledge, stigma, lived experience of the disease in adolescents, effects on autonomy, the concept of psychosis, impact on social relations, local lay referral system, any harmful practices used by TSHs, and triggers, barriers and facilitators to seeking formal healthcare.

The findings of the ethnography will feed into the topic guides for semistructured interviews (SSIs) and focus group discussions (FGDs) that will be undertaken with parents, especially mothers, who have a critical role in initiating psychiatric treatment for their child with FEP. We will conduct SSIs (n=~25) with both patients and carers and six FGDs with 8–12 participants, including TSHs, PCPs, psychiatrists and other health workers. These SSIs and FGDs will be conducted in the local Pashto language to explore perceptions, understandings and experiences with FEP of patients and carers, involvement of young persons in decision-making, ways to improve early detection of psychosis, views regarding the nature of symptoms in young people, experiences of receiving treatment from TSHs, barriers and facilitators to early treatment, training needs for TSHs and professionals and best methods to deliver the intervention.

This development phase will inform the development of THE HOPE intervention (see below), which will be evaluated in a cluster feasibility RCT.

### Study design

We will use a pragmatic cluster pilot RCT to test the feasibility and acceptability of the intervention. The study will be reported using the Consolidated Standards of Reporting Trials extension for randomised pilot and feasibility trials.^20^

### Study setting

The study will be carried out in Peshawar district, the capital city of KP province in Pakistan. District Peshawar has a population of about 4 million. The district has 93 union councils (UCs) as basic administrative divisions. Each UC has, on average, a population of about 20 000 and is served by a primary healthcare centre called Basic Health Unit (BHU), providing essential primary healthcare services. The mental health services are provided mainly in three teaching hospitals in Peshawar with about 20 qualified psychiatrists.

### Randomisation

Randomisation will occur at the UC level and be allocated using a 1:1 ratio to either the intervention arm (THE HOPE) or enhanced treatment as usual (ETAU) and stratified by urban/rural setting.

### Sample size

This being a feasibility study, we do not provide a power calculation as there is no proposal for formal hypothesis testing, and the sample size focuses on the required precision of feasibility parameters in line with recommendations for pilot and feasibility studies.^21^ FEP has a relatively low incidence of about 26.6 per 100 000 person-years.^22^ In order to obtain an adequate sample size to measure feasibility outcomes, we will include all UCs in district Peshawar (n=93) in the sample, allocated to ETAU and THE HOPE arm in a 1:1 ratio. We will aim to recruit a minimum of 90 patients (45 in each arm) over a 12-month period. We believe this will help us to achieve reasonable precision of feasibility estimates, for example, for evaluation of intervention fidelity and participant retention in the study (as a proportion). This will enable the 90% one-sided lower confidence bound to be derived to a margin of error of 0.1 for single-arm evaluation and 0.07 for overall sample evaluation. This fits the criteria for sample size justification and calculation recommendations for pilot and feasibility studies.^23^

### The intervention and control arms

#### The intervention arm

THE HOPE intervention arm will receive THE HOPE intervention in addition to ETAU. THE HOPE is an organisational/service-level intervention with the following essential components (see figure 1):

A cascade model of training and task-shifting from psychiatrists to PCPs and from PCPs to TSHs for early detection and treatment of FEP in adolescents.Linking TSHs and PCPs with mental health professionals for early identification and referral of FEP and establishing community pathways for effective management of FEP.

**Figure 1 F1:**
[figure not shown]
The HOPE flow diagram. DUP, duration of untreated psychosis; MhGAP, Mental Health Gap Action Programme; RCT, randomised controlled trial; THE HOPE, Traditional HEalers working with primary care and mental Health for early interventiOn in Psychosis in young pErsons.

A group of four TSHs will be linked with one PCP working in the nearest BHU. PCPs trained in early identification and referral of FEP in adolescents in Work Package 1 (WP1) will work collaboratively with the TSH and psychiatrist supervising the treatment.

The TSHs and PCPs will work collaboratively in establishing care pathways for the optimum management of FEP in young persons.

The cascade training for early identification and management will consist of the following:

#### Training for psychiatrists

First, a team of psychiatrists with extensive experience in early intervention in psychosis and child and adolescent psychiatry in the UK and Pakistan will train local psychiatrists in the early detection and treatment of FEP. We will train two psychiatrists who will act as master trainers (MTs). These MTs, in turn, will train PCPs. We will use face-to-face teaching, case studies and direct clinical supervision. The training will be based on recent guidelines^24 25^ on the early detection and management of psychosis in young people^24^ adopted for the local settings. Mental Health Gap Action Programme (MhGAP) guidelines on Training of Trainers^26^ will be used for training MTs, and quality assured by Khyber Medical University (KMU).

#### Training for PCPs

Second, these MTs will train PCPs using interactive methods. PCPs in both arms will be trained in the MhGAP treatment guidelines, while those in the intervention arm will receive additional training in the early detection and management of FEP by MTs, as described above.

#### Training for TSHs

Third, these PCPs will train TSHs for identification, referral and working collaboratively with PCPs and health services for effective management of FEP. The information gained from ethnographic and qualitative studies will inform the contents, format and methodology for training TSHs. Based on our experience of working with traditional healers in the STOPS+ Programme,^10^ the training will mainly focus on the following topics: overcoming barriers to working with psychiatric services, symptoms and signs of FEP and differentiating these from normal behaviours expected in adolescence, attitudes and behaviours towards people with psychosis, avoiding harmful practices, respecting individual autonomy, preventing gender-based discrimination and information about referral pathways.

The training will be delivered in a workshop.

Two main educational tools used in workshops will be (1) case vignettes of typical patients for identification of suspected cases of FEP, which we have successfully used in our previous research with lay health workers, and (2) a video in the local language that will deliver the key messages on topics mentioned above.

We have used this model of task-shifting and cascade training in our previous research^27^ and will use a similar approach in implementing the intervention.

#### Control arm: ETAU

This arm will include treatment as usual, enhanced by MhGAP training for PCPs and generic training for TSHs about good mental health. Training will be of similar duration to that for the intervention but will not include content specifically related to early intervention in psychosis but will include generic training for psychosis care included in MhGAP. ETAU provided in the control clusters will include the treatment received by patients’ routine healthcare setting, which includes treatment provided by a psychiatrist in the outpatient clinics of the psychiatry department of the local hospital and brief counselling about the treatment and outcome of the disorder.

A group of four TSHs will be linked with one PCP working in the nearest BHU. The PCPs in the control group will be trained in the general management of psychosis provided in the MhGAP manual.

### Identification of the PCPs and TSHs

We will select 20 TSHs who will be linked with five PCPs working in the local primary healthcare centres in each arm of the study. A group of five TSHs will be linked with one PCP working in the nearest primary healthcare centre. The PCPs will be randomly selected in both intervention and control arms and will be linked to TSHs. The selection will be made by the Department of Family Medicine at KMU.

Our previous work in this area has identified three types of TSH: (1) Pirs (spiritual leaders in Sufi tradition) with well-established shrines, (2) imams, spiritual leaders based in mosques and (3) traditional healers who practise traditional methods such as (taweez) alms or herbs. After consultations with community elders, 20 TSHs in each arm will be selected based on (1) an established reputation for treating mental health problems and not using harmful practices, and (2) willingness to work with the healthcare system.

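### Ninety-three union councils are randomised but each arm works through five PCPs and 20 TSHs, and the stated margins of 0.1 and 0.07 make no allowance for that grouping

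*Protocol article*

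**What the plan says.** All points are in the protocol article.

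- **Randomised unit.** Under Randomisation: "Randomisation will occur at the UC level and be allocated using a 1:1 ratio". Under Sample size: "we will include all UCs in district Peshawar (n=93) in the sample". Study setting gives each UC an average of about 20 000 people and a Basic Health Unit (BHU).
- **Providers.** The section Identification of the PCPs and TSHs sets the numbers per arm: "We will select 20 TSHs who will be linked with five PCPs working in the local primary healthcare centres in each arm of the study".
- **Group size.** The intervention-arm text says "A group of four TSHs will be linked with one PCP working in the nearest BHU", and the control-arm text says the same. Identification of the PCPs and TSHs says "A group of five TSHs will be linked with one PCP working in the nearest primary healthcare centre".
- **Patients.** Under Participant eligibility criteria, they may live in any UC of the district. Under Recruitment, the cluster's allocation fixes the treatment path. A patient who presents to a healer of the other arm is offered the nearest healer of his or her own arm, and otherwise is not included.
- **Precision.** Sample size sets a minimum of 90 patients, 45 per arm, and names fidelity and retention as proportions to be estimated: "This will enable the 90% one-sided lower confidence bound to be derived to a margin of error of 0.1 for single-arm evaluation". The corresponding figure for the whole sample is 0.07. No assumed proportion, ICC or design effect accompanies these figures.
- **Population.** Study setting: "District Peshawar has a population of about 4 million".
- **Use of the cluster.** Quantitative analysis will estimate average cluster size and its variation, and the Green criterion is glossed as about 1.5 recruits per UC.

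**The concern.** The unit that is randomised (UC) is not the unit through which care is delivered (a PCP with linked healers). This has two consequences.

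First, cluster size, its variation and recruits per UC are meant to inform the main trial. If most UCs have no study provider, these figures average over places with and without local delivery, and it is unclear what they describe. The article does not say how a UC without a provider receives its allocated arm.

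Second, the margins are the only quantitative justification of the sample size. Quantitative analysis defines treatment fidelity as the proportion of intervention-arm patients who have the planned pathway. That result depends on how a handful of PCP–TSH groups work, so patients of the same group may resemble one another. Retention may follow the same grouping. An interval that treats the 45 patients as independent would then be too narrow.

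Two pairs of counts also disagree: healers per PCP, and district population against UC count times UC size. The first of these changes the number of groups on which the precision rests.

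**Working it through.** **1. Reproduce the stated margins.** Inputs from Sample size: n = 45 and n = 90, 90% one-sided bound, so z = 1.2816. The article gives no proportion; p = 0.5 is the worst case. Margin = z × √(p(1 − p)/n).

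- Single arm: 1.2816 × √(0.25/45) = 0.0955, stated as 0.1.
- Overall: 1.2816 × √(0.25/90) = 0.0675, stated as 0.07.

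Both figures reproduce with independent patients and no design effect. A two-sided 90% interval would give 0.123 and 0.087, which does not match.

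**2. Count the UCs without a study provider.** 93 UCs at 1:1 gives 46 or 47 per arm.

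- PCPs: five can sit in at most five UCs, so at least 46 − 5 = 41 per arm have none. Over both arms, at most 10/93 = 10.8% of UCs have one.
- TSHs: even if all 20 were in different UCs, at least 46 − 20 = 26 per arm have none.

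**3. Add clustering by provider group.** Patients per group: m = 45/5 = 9, assuming equal groups and every patient belonging to one. DE = 1 + (m − 1) × ICC = 1 + 8 × ICC, and each margin is multiplied by √DE. The article gives no ICC, so the values below are assumptions.

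| ICC | DE | Single arm, p = 0.5 | Overall, p = 0.5 | Single arm, p = 0.8 | Overall, p = 0.8 |
|---|---|---|---|---|---|
| 0 | 1.00 | 0.0955 | 0.0675 | 0.0764 | 0.0540 |
| 0.02 | 1.16 | 0.1029 | 0.0727 | 0.0823 | 0.0582 |
| 0.05 | 1.40 | 0.1130 | 0.0799 | 0.0904 | 0.0639 |
| 0.10 | 1.80 | 0.1282 | 0.0906 | 0.1025 | 0.0725 |

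**4. Find the ICC at which the stated margins fail.** Tolerated DE = (stated margin / independent margin)², and ICC = (DE − 1)/8.

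| p | Tolerated DE, single arm (0.1) | ICC | Tolerated DE, overall (0.07) | ICC |
|---|---|---|---|---|
| 0.5 | 1.096 | 0.012 | 1.074 | 0.009 |
| 0.7 | 1.305 | 0.038 | 1.279 | 0.035 |
| 0.8 | 1.712 | 0.089 | 1.678 | 0.085 |

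**5. Vary the clustering unit (p = 0.5).**

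- By single healer, m = 45/20 = 2.25: ICC 0.05 to 0.10 gives 0.099 to 0.101 per arm and 0.070 to 0.072 overall.
- By UC of residence, m = 90/93 = 0.97: DE is about 1 and the margins do not change.
- By groups of five healers, 20/5 = 4 groups per arm and m = 45/4 = 11.25: ICC 0.05 to 0.10 gives 0.118 to 0.136 per arm and 0.083 to 0.096 overall.

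**6. Check the conflicting counts.**

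- 20 healers over five PCPs is 20/5 = 4 each. Five healers for each of five PCPs would need 5 × 5 = 25.
- 93 × 20 000 = 1.86 million, against about 4 million stated; 4/1.86 = 2.15.

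**The case against.** The strongest reply concerns what the mismatch implies. A reader might infer that most clusters receive no intervention. The article does not support that. Patients may come from any UC, those who present to a wrong-arm healer can be redirected to one of their own arm, and recruitment also runs through mental health services. What remains is that most UCs have no local study provider, and the redirection rule describes patients travelling to a provider rather than how the UC itself is served.

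A reader might also infer that 0.1 and 0.07 are simply wrong and should be replaced by larger figures. That does not follow either. They are correct for independent patients at the worst-case p. The progression thresholds for retention are 70% and 80%, and near p = 0.8 there is room for an ICC of about 0.085. Even at p = 0.5, an ICC of 0.02 gives 0.103 and 0.073, which round to the stated values. Patients recruited through mental health services may belong to no PCP–TSH group, which would weaken the clustering. This part of the reply stands, and it rules out a single replacement figure. It does not remove the need to state p and an ICC, because fidelity has no stated expected value and is delivered through very few groups.

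The population conflict might be read as undermining the recruitment targets. The article justifies 90 by precision and does not derive it, or the 130 cut-off, from a case pool, so the conflict changes no stated figure. A link to the nearest BHU might suggest cross-arm pairing, but providers are selected within each arm, so same-arm linkage is already largely implied.

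A journal article may leave the mapping of UCs to providers to the full protocol. The counts printed here nevertheless conflict with one another.

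**Conclusion.** The concern holds in a limited form. By the article's own counts, at least 41 of about 46 UCs per arm have no study PCP and at least 26 have no study TSH. This needs no assumption beyond a PCP or healer being based in one UC. The two conflicts in the counts likewise stand on the text alone.

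The precision statement omits clustering by provider group. How much that matters depends on assumptions the documents do not supply: the ICC, the proportion, and whether outcomes cluster by PCP group, by healer or by UC. With nine patients per PCP group, the stated margins are exceeded above an ICC of about 0.01 at p = 0.5, 0.035 at p = 0.7 and 0.085 at p = 0.8. The likely effect is a modest loss of precision. In a feasibility trial without hypothesis testing, this affects how firmly fidelity and retention can be judged against their targets; it does not invalidate the design.

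**What to change.** 1. Keep the UC as the randomised unit, but compute the intervals for fidelity and retention allowing for clustering by PCP–TSH group. Say how patients with no link to a study group are handled. Five groups per arm will say little about the ICC, so show results over a range of values.
2. Restate the margins with the assumed proportion and an ICC range, for example as in the working, instead of one replacement pair.
3. Report recruitment per PCP–TSH group, and separately for UCs with and without a study provider, so that average cluster size and the benchmark of about 1.5 per UC can be interpreted.
4. State which UCs have a study provider and how the others receive their allocated arm.
5. Reconcile four with five TSHs per PCP, and the district population with the number and average size of UCs.

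The cost is protocol wording, some extra tabulation and a slightly less favourable precision statement. No additional patients or staff are needed.
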